## 200 **4. Outcomes**

### 201 **4.1 Primary Efficacy Outcome**

202 Proportion of patients with functional independence ( $mRS \leq 2$ ) at 3 months after randomization.

### 203 **4.2 Secondary Efficacy Outcomes**

- 204 1. Proportion of recurrent stroke (ischemic stroke and intracerebral hemorrhage) at 3 months and 12 months
- 205 after randomization;
- 206 2. Proportion of patients with functional independence ( $mRS \leq 2$ ) at 12 months after randomization;
- 207 3. Proportion of patients with no or minimal disability ( $mRS \leq 1$ ) at 3 months and 12 months after
- 208 randomization;
- 209 4. Change in NIHSS score at 3 months after randomization;
- 210 5. Proportion of composite cerebrovascular events (ischemic stroke, intracerebral hemorrhage, myocardial
- 211 infarction, and vascular death) at 3 months and 12 months after randomization;
- 212 6. Difference of EuroQoL Group 5-Dimension (EQ-5D) score at 3 months and 12 months after
- 213 randomization;
- 214 7. Change in Barthel Index (BI) score at 3 months and 12 months after randomization;
- 215 8. Difference of platelet counts and coagulation indicators (prothrombin time, and activated partial
- 216 thromboplastin time) at 3 months after randomization.

### 217 **4.3 Primary Safety Outcome**

218 Incidence of serious adverse events (SAEs) within 3 months of treatment.

### 219 **4.4 Secondary Safety Outcomes**

- 220 1. Incidence of symptomatic intracranial hemorrhage within 3 months of treatment;
- 221 2. Incidence of all-cause mortality within 3 months of treatment;
- 222 3. Incidence of AEs within 3 months of treatment.

## 223 **5. Study Design**

224 **5.1 Study Type**

225 A randomized, double-blind, placebo-controlled, multi-center trial.

226 **5.2 Randomization**

227 Eligible patients will be randomized into an XST group and a control group at a ratio of 1: 1 to receive XST  
228 or placebo.

229 ***XST group:***

230 XST, 60 mg/capsule, 120 mg per time, twice daily

231 ***Control group:***

232 XST placebo, 60 mg/capsule, 120 mg per time, twice daily

233 **6. Study Plan and Procedures**

234 Study period: From November 2017 to December 2021;

235 Duration of treatment: 3 months;

236 Study period for patients included in the trial: 12 months;

237 The endpoint of the whole trial is defined as the last visit of the last patient enrolled in the trial.

238 **6.1 Visit Schedule**

| Measures                               | Randomization/Day
1 | 1 month | 3 months | 6 months | 12 months |
|----------------------------------------|------------------------|---------|----------|----------|-----------|
| Demographic characteristics            | X                      |         |          |          |           |
| Presenting complaint                   | X                      |         |          |          |           |
| Physical examinations                  | X                      | X       | X        |          |           |
| mRS                                    | X                      | X       | X        | X        | X         |
| Past medical history                   | X                      |         |          |          |           |
| NIHSS                                  | X                      | X       | X        |          |           |
| Head CT/MRI                            | X                      |         |          |          |           |
| ASPECTS                                | X                      |         |          |          |           |
| Laboratory tests                       | X                      |         | X        |          |           |
| ECG                                    | X                      |         |          |          |           |
| Verifying inclusion/exclusion criteria | X                      |         |          |          |           |
| Signed written informed consent        | X                      |         |          |          |           |
| Randomization                          | X                      |         |          |          |           |

| Measures                | Randomization/Day 1 | 1 month | 3 months | 6 months | 12 months |
|-------------------------|---------------------|---------|----------|----------|-----------|
| Compliance              |                     | X       | X        |          |           |
| TOAST classification    | X                   |         |          |          |           |
| EQ-5D scale             | X                   | X       | X        | X        | X         |
| BI                      | X                   | X       | X        | X        | X         |
| Concomitant medications |                     | X       | X        | X        | X         |
| Capsule administration  | X                   | X       | X        |          |           |
| AEs/SAEs                |                     | X       | X        | X        | X         |

#### 6.1.1 Visit 1: Screening/Randomization Day (Day 1)

- Signed written informed consent;
- Demographic characteristics;
- Relevant medical history and surgical history;
- Vital signs and physical examination;
- Head CT/MRI;
- Trial of Org 10172 in Acute Stroke Treatment classification;
- 12-lead electrocardiograph (ECG);
- Alberta Stroke Program Early CT Score, NIHSS, mRS, EQ-5D , and BI scores;
- Laboratory tests: hematology (including white blood cell count, neutrophil count, hemoglobin, and platelet count), urinalysis (including white blood cell, ketone bodies, and occult blood), coagulation (including prothrombin time, and activated partial thromboplastin time), hepatic and renal functions (including blood creatinine, and serum aminotransferase), electrolyte (including K+, and Na+), fasting serum glucose, and lipid (triglyceride, and total cholesterol);
- Current medications;
- Patients will be advised to start the corresponding treatment on the day when the patient meets the inclusion criteria. If the patient does not meet the inclusion criteria, the reason for the exclusion will be recorded in Patient Screening Records;
- Drug distribution.

The test results obtained at Visit 1 will be used as the baseline values;

#### 6.1.2 Visit 2: 1 Month after Randomization, Face-To-Face Follow-Up (Month 1 ± 3 days)

- Vital signs and physical examination;
- NIHSS, mRS, EQ-5D, and BI scores;
- AEs and SAEs;
- Medication adherence;

- 264 • Current medications;
- 265 • Cardiovascular and cerebrovascular events: new strokes (ischemic stroke and intracerebral hemorrhage),
- 266 and new composite cerebrovascular events (ischemic stroke, intracerebral hemorrhage, myocardial
- 267 infarction, and vascular death).
- 268 **6.1.3 Visit 3: 3 Months after Randomization, Face-To-Face Follow-Up (Month 3 ± 7 days)**
- 269 • Vital signs and physical examination;
- 270 • NIHSS, mRS, EQ-5D, and BI scores;
- 271 • Laboratory tests: hematology (including white blood cell count, neutrophil count, hemoglobin, and platelet
- 272 count), coagulation (prothrombin time and activated partial thromboplastin time), hepatic and renal
- 273 functions (blood creatinine and serum aminotransferase);
- 274 • AEs and SAEs;
- 275 • Medication adherence;
- 276 • Current medications;
- 277 • Cardiovascular and cerebrovascular events: new strokes (ischemic stroke and intracerebral hemorrhage),
- 278 and new composite cerebrovascular events (ischemic stroke, intracerebral hemorrhage, myocardial
- 279 infarction, and vascular death).
- 280 **6.1.4 Visit 4: 6 Months after Randomization, Face-To-Face or Telephone Call Follow-Up (Month**
- 281 **6 ± 7 days)**
- 282 • mRS, EQ-5D, and BI scores;
- 283 • AEs and SAEs;
- 284 • Current medications;
- 285 • Cardiovascular and cerebrovascular events: new strokes (ischemic stroke and intracerebral hemorrhage),
- 286 and new composite cerebrovascular events (ischemic stroke, intracerebral hemorrhage, myocardial
- 287 infarction, and vascular death).
- 288 **6.1.5 Visit 5: 12 Months after Randomization, Face-To-Face or Telephone Call Follow-Up (Month**
- 289 **12 ± 7 days)**
- 290 • mRS, EQ-5D, and BI scores;
- 291 • AEs, SAEs, and endpoints;
- 292 • Current medications;
- 293 • Cardiovascular and cerebrovascular events: new strokes (ischemic stroke and intracerebral hemorrhage),
- 294 and new composite cerebrovascular events (ischemic stroke, intracerebral hemorrhage, myocardial
- 295 infarction, and vascular death).
- 296 **6.2 Protocol Compliance**
- 297 **6.2.1 Withdrawal Determined by the Investigator**
- 298 1. Patients undergoing allergic reactions or SAEs will withdraw from the study as judged by the physician;
- 299 2. The patient's symptoms worsened after medication, and in order to protect the patient, the patient was
- 300 withdrawn from the study and received other effective treatment;
- 301 3. Patients experience some comorbidities, complications, or special physiological changes during the study,
- 302 affecting the efficacy and safety evaluations;

4. Patients with poor compliance during the study, i.e., underdosing by less than 70% or overdosing by more than 130% of the required doses;
5. Patients who are midway breaking the blindness during the study for any reasons;
6. Patients who are considered not suitable to continue the study as judged by the investigator.

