### **7.6.3 Procedure of IMP Discontinuation for Patients**

Patients who have permanently discontinued the IMPs will receive conventional therapies, and, if applicable, continue the regular visits as follows: Patients who have decided to discontinue the IMPs will be asked for reasons and whether they have experienced any AE. This information will be verified and recorded by investigators in the corresponding positions in the CRF. Information of all patients will be collected as much as possible during the whole study period, especially all the potential endpoint events. The complete withdrawal from study (withdrawal of the informed consent) may have a direct impact on the potential validity of the data, so it will be avoided as much as possible. Patients may continue to participate in the study according to the various following options if the patient has permanently discontinued the administration of the IMPs before the end of the study:

1. Patient agrees to participate in discontinuation visits and continues to attend visits in person.

This is the most ideal option, but the consent from the patients toward treatment discontinuation will be obtained before implementation. If the patient agrees, he/she will receive a premature treatment discontinuation visit (PTDV) on the day of discontinuation. After PTDV, the patient will also participate in the subsequent visits as scheduled, and data collection will be continued as per the protocol.

2. Patient refuses to attend visits in person but accepts to receive the follow-up by other means.

If the patient refuses to attend visits in person but accepts to receive the follow-up by other means, he/she will receive PTDV on the day of discontinuation. The subsequent visits before the end of the study will be conducted by other means (regular phone calls, and contact at the end of the study), which are applicable to patients who have not withdrawn the informed consent or withdrawn from the study.

3. Patient rejects follow-up by any means.

The patient rejects follow-up by any means, that is, the patient formally withdraws from the study and withdraws the informed consent. This decision will be recorded, and when the double-blind study period scheduled for such patients ends (3 months after the randomization), the survival status information of the patient will be collected via public channels pursuant to local laws. This plan will be avoided as much as possible.

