#### **13.1 Analysis Cohorts**

##### **13.1.1 Modified Intention-To-Treat Cohort**

According to the basic principle of intention-to-treat analysis, all patients after randomization who received at least one record for drug administration and efficacy evaluation will be included in the modified intention-to-treat cohort. During analysis with the modified intention-to-treat cohort, missing values will be estimated using the last observation carried forward method. The modified intention-to-treat population will be the primary population for efficacy evaluation in this study.

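### The month-3 visit that carries the primary endpoint has no written remote fallback for the mRS in patients still on capsules, so a patient not seen in person has an older score carried forward

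*Protocol*

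**What the plan says.** Protocol 4.1 defines the primary outcome as the proportion with mRS 2 or less at 3 months after randomization. Section 6.1.3 schedules its collection at "Visit 3: 3 Months after Randomization, Face-To-Face Follow-Up (Month 3 ± 7 days"). The visit before it is also in person only: "Visit 2: 1 Month after Randomization, Face-To-Face Follow-Up (Month 1 ± 3 days"). No alternative mode is written for either.

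The later visits differ. Section 6.1.4 reads "Visit 4: 6 Months after Randomization, Face-To-Face or Telephone Call Follow-Up" and 6.1.5 reads "Visit 5: 12 Months after Randomization, Face-To-Face or Telephone Call Follow-Up". Both collect mRS, EQ-5D and BI, and the month-12 mRS feeds secondary outcomes 2 and 3 in section 4.2.

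Section 7.6.3 adds a remote option headed "Patient refuses to attend visits in person but accepts to receive the follow-up by other means", which includes telephone calls. Its options apply "if the patient has permanently discontinued the administration of the IMPs before the end of the study". Section 7.6.2 likewise continues telephone follow-up after the drug has been stopped.

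For the modified intention-to-treat cohort, which is primary for efficacy, section 13.1.1 states that "missing values will be estimated using the last observation carried forward method".

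**The concern.** Two things look wrong together. First, the protocol accepts a telephone mRS for secondary efficacy outcomes and for patients who have stopped treatment, but writes no such route for patients on treatment at the one time point for which the trial was sized. The availability of a remote month-3 score thus depends on treatment status, a post-randomization fact.

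Second, not being seen in person is probably related to disability, which is what the mRS measures. The value used instead comes from month 1 or Day 1. A patient with mRS 2 or less at month 1 who then has a disabling recurrence and is not seen at month 3 would be counted as independent. A patient who recovers after month 1 and is not seen would be counted as dependent. A telephone call could have recorded the actual state in both cases. An analysis plan cannot repair this later, because the score was never collected.

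**Working it through.** **The protocol's own figure.** Inputs from sections 13 and 13.3: control rate p0 = 0.45, XST rate p1 = 0.45 × 1.12 = 0.504, two-sided alpha 0.05, power 0.80, 1:1 allocation, 10% loss.

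n per group = [1.960 × √(2 × 0.477 × 0.523) + 0.842 × √(0.45 × 0.55 + 0.504 × 0.496)]² / 0.054² = 1342. Then 1342 / 0.9 = 1492 after rounding up. Both stated figures are reproduced. The fallback does not change them.

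**Routes to a month-3 mRS as written.**

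| Patient at month 3 | In person | Telephone |
|---|---|---|
| On capsules | yes (6.1.3) | none written |
| Capsules permanently stopped | yes (7.6.3, option 1) | yes (7.6.2; 7.6.3, option 2) |
| Any patient, months 6 and 12 | yes | yes (6.1.4, 6.1.5) |

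**Effect under carry-forward.** The protocol gives none of the following inputs, so they are assumptions. Let m be the share of patients with a true month-3 mRS above 2 who are not seen, and q the share of those whose carried score is 2 or less. The analysed rate in an arm is p + (1 − p) × m × q.

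*Equal m and q in both arms.* The difference becomes (p1 − p0) × (1 − m × q). With q = 0 it stays at 5.4 points. With q = 20% and all 1500 per group analysed:

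| m | Missing in controls (0.55 × m) | Difference | Power |
|---|---|---|---|
| 0 | 0 | 5.40 points | 0.842 |
| 5% | 2.8% | 5.4 × 0.990 = 5.35 points | 0.834 |
| 10% | 5.5% | 5.4 × 0.980 = 5.29 points | 0.827 |
| 18% | 9.9% | 5.4 × 0.964 = 5.21 points | 0.814 |

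The last row puts about the whole 10% loss allowance on this mechanism.

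*Different m by arm, q = 20%.* The shift in points is 100 × q × [(1 − p1) × m1 − (1 − p0) × m0], where m1 is XST and m0 is control.

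- m0 = 10%, m1 = 5%: 0.2 × (2.48 − 5.50) = −0.60, so 5.4 becomes 4.80.
- m0 = 5%, m1 = 10%: 0.2 × (4.96 − 2.75) = +0.44, so 5.4 becomes 5.84.
- m0 = 20%, m1 = 10%: 0.2 × (4.96 − 11.00) = −1.21, so 5.4 becomes 4.19.
- m0 = 10%, m1 = 20%: 0.2 × (9.92 − 5.50) = +0.88, so 5.4 becomes 6.28.

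If there is no true effect and both arms have 45%, the false difference is 100 × 0.2 × 0.55 × (m1 − m0). That is 0.55 points for a 5-point gap in m and 1.1 points for a 10-point gap.

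These runs cover one direction of error only (dependent patients carried as independent). Errors the other way would add to or offset them.

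**The case against.** A reader might infer that patients too disabled to travel lose their primary outcome. The text does not support that. Section 13.1.1 keeps them in the analysis with an earlier score, and for someone persistently at mRS 4 or 5 that score will usually also exceed 2, so the binary endpoint is unchanged. The protocol also does not say that the visit must take place at the centre, and it does not exclude a home or ward visit. Only a patient without a qualifying efficacy record could leave the cohort, and whether the Day-1 mRS qualifies is not stated.

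A late in-person score is not barred from the primary cohort either. Section 13.1.2 treats serious departure from the window as a per-protocol matter only.

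The recurrence example is narrower than it looks. Such an event may lead to stopping capsules, which opens the telephone route, or to withdrawal under 6.2.1, which is a different source of loss. What remains is the patient who changes status, stays on capsules and cannot be seen anywhere in person. The protocol gives no means of sizing that group.

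An in-person month-3 visit is also a reasonable design. It needs NIHSS, physical examination, laboratory tests and a capsule count, and a single rating mode has value.

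All of this limits the size of the problem. It does not supply the missing route. The tests explain why the visit is in person, but they do not explain why the mRS should go uncollected when the visit cannot happen.

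**Conclusion.** The point holds as a gap in data collection at the primary time point, and it should be fixed. For a patient on capsules who is not seen in person, the protocol replaces an obtainable month-3 mRS with a month-1 or Day-1 value, while accepting telephone scores elsewhere.

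The size cannot be derived from the protocol. With equal non-attendance in the two arms, the assumed scenarios leave 5.21 to 5.35 of the planned 5.4 points, which is small. With unequal non-attendance the shift can be larger and can favour either arm, but nothing in the protocol says that attendance will differ.

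Two stronger conclusions are tempting and not supported. One is that a telephone fallback would buy back power by recovering part of the 10% loss allowance. Section 13.3 does not attribute that allowance to visit mode, and carry-forward keeps patients with an efficacy record in the analysis. The other is that a definite share of the planned benefit is lost because deterioration with a missed visit is commoner in controls. That needs an arm difference for which the protocol gives no source.

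**What to change.** Add to 6.1.3: if an in-person assessment, at the centre or elsewhere, cannot be done within the window, the mRS is taken by telephone from the patient or caregiver, together with EQ-5D, BI, AEs/SAEs and vascular events, whether or not capsules are still being taken. Record the mode of assessment. State that this mRS counts in the primary outcome in place of a carried-forward value. Keep NIHSS, physical examination and laboratory tests in person. Add a sensitivity analysis of the primary outcome restricted to face-to-face mRS scores.

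The cost is a short addition to 6.1.3, one CRF field and one extra analysis. The sample size does not change. The downside is slightly more rating error in the minority rated by telephone, and their mode will probably be related to disability. The fallback applies only where the in-person score would otherwise be missing, and the recorded mode with the sensitivity analysis makes its influence visible.

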#### 7.4.1 Contraindicated Concomitant Medications, Food Products, and Health Care Products

During the study (including the oral administration period of XST/XST placebo), the use of traditional Chinese medicinal products, food products, and health care products, containing panax notoginseng, will be disallowed. Using the following drugs, food products and health care products containing panax notoginseng constitutes a violation of the protocol, the IMPs will be discontinued in such cases and the reasons will be recorded, but the visit at Month 3 will be completed.

Traditional Chinese medicinal products containing panax notoginseng include: Xueshuantong capsules, Xueshuantong injections, Panax notoginseng saponins tablets, Panax notoginseng saponins capsules, Compound Danshen dripping pills, Sanqi Shangyao tablets, Sanqitongshu capsules, Sanqi Xueshangning capsules, and Yanghuo Sanqi capsules.

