#### **7.6 Discontinuation of IMPs**

IMPs will be administered as continuously as possible, but patients may discontinue the study treatment and evaluation at any time. When an IMP is discontinued, a decision for allowing temporary discontinuation is reached, if not, permanent discontinuation will be the last resort. Any drug discontinuation will be completely recorded on the corresponding page of the CRF. Patients will participate in the trial as long as possible under any circumstances. Pregnancy will lead to the permanent discontinuation of the trial under any circumstances.

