##### **7.6.2 Permanent Discontinuation of Study Treatment**

1. Decided by patients. Patients may terminate the treatment freely at any time without affecting their further treatment.
2. Decided by investigators. Including but not limited to the following:
  - 1) Mistaken enrollment that does not meet the Inclusion Criteria/Exclusion criteria, and will put the patient at a higher risk;
  - 2) AE is considered to be related to the study treatment and the investigator believes that continuing treatment may pose a higher risk;
  - 3) Poor compliance with the protocol;
  - 4) Pregnancy.

Discontinuation of IMPs does not mean discontinuation of follow-up or withdrawal from study. The study evaluation and telephone follow-up for all patients will be continued after the drug discontinuation.

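### Section 6.2.1 withdraws patients from the study for SAEs, allergy or worsening without saying that follow-up continues, while section 7.6.2 treats overlapping events as a drug stop with evaluation continued

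*Protocol*

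**What the plan says.** Section 6.2.1 of the protocol lists six grounds for withdrawal decided by the investigator. Item 1 reads "Patients undergoing allergic reactions or SAEs will withdraw from the study as judged by the physician". Under item 2, a patient whose symptoms worsen on medication is "withdrawn from the study and received other effective treatment". Item 4 begins "Patients with poor compliance during the study" and gives dose limits. Only items 1 and 2 say that the patient leaves the study; items 3 to 6 are withdrawals by virtue of the heading alone. The section is silent on later visits and does not refer to 7.6.

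Section 7.6.2 gives the investigator's reasons for stopping study drug permanently. They include an AE judged related to treatment, where continuing would raise the risk, and "Poor compliance with the protocol". It then states: "Discontinuation of IMPs does not mean discontinuation of follow-up or withdrawal from study", and continues evaluation for all patients. Section 7.6 says "Patients will participate in the trial as long as possible under any circumstances", and 7.6.3 says "Information of all patients will be collected as much as possible during the whole study period". Section 7.4.1 stops the drug after a prohibited product is used, "but the visit at Month 3 will be completed".

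Section 7.7 gives permanent discontinuation of the drug as one example of withdrawing from the study, which is the opposite of what 7.6.2 says.

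**The concern.** One event can be handled in two ways. Poor compliance, or an SAE that is also a related AE, is a withdrawal under 6.2.1 and a drug stop with continued evaluation under 7.6.2. A site that opens 6.2.1 first finds nothing there that sends it to 7.6.

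The primary outcome is mRS of 2 or less at 3 months, and the grounds in items 1 and 2 are related to it. If visits stop for these patients, the month-3 value is missing because the patient did badly, and section 13.1.1 replaces it with the last recorded value. That value may come from before the event that led to withdrawal. An analysis plan cannot recover a visit that was never made, so the matter has to be settled in the protocol text.

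**Working it through.** **1. The two lists side by side**

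| Event | Section 6.2.1 | Section 7.6.2 |
|---|---|---|
| SAE or allergic reaction | Leaves the study, at the physician's judgement (item 1) | Related AE with higher risk if continued: drug stopped, evaluation continues |
| Worsening on medication | Leaves the study (item 2) | Not named; the list is open-ended |
| Poor compliance | Under the withdrawal heading (item 4) | Drug stopped, evaluation continues |

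**2. Does another section secure the month-3 mRS after a 6.2.1 withdrawal?**

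- 7.4.1 keeps the month-3 visit, but only for use of panax notoginseng products.
- 8.3 keeps visits going, but only for patients enrolled in error.
- 7.6.2 and 7.6.3 keep evaluation going for patients who stop study drug. They cover a 6.2.1 patient only if 6.2.1 is read as a drug stop.
- The survival check in 7.6.3 and 7.7 is written for withdrawn consent, and it yields vital status, not mRS.
- 10.5 follows an unresolved SAE after early withdrawal, but only the event itself.

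None of them does so expressly.

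**3. What would stand in for a lost value**

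The visit schedule (6.1) has mRS at day 1 and month 1 before month 3. Section 7.6.3 adds a discontinuation visit, but the protocol does not list its content. Under last observation carried forward (13.1.1):

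- A patient with mRS of 2 or less at month 1 who then worsens and is not independent at month 3 is wrongly counted as a success.
- A patient whose carried mRS is above 2, and who is also above 2 at month 3, is classified correctly.
- A patient withdrawn under items 4 to 6 who improves afterwards may wrongly be counted as a failure.
- A patient withdrawn before month 1 with no mRS at the discontinuation visit carries the day-1 value or, if the efficacy evaluation required by 13.1.1 must follow dosing, leaves the primary cohort.
- An mRS taken at the discontinuation visit would lie closer to the event and shrink the error.

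**4. Scale**

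The protocol's own figure first (section 13.3): control 0.45, XST 0.45 × 1.12 = 0.504, two-sided alpha 0.05, power 0.80. The pooled-variance formula without continuity correction, n = [1.960 × √(2 × 0.477 × 0.523) + 0.8416 × √(0.45 × 0.55 + 0.504 × 0.496)]² / 0.054², gives 1342 per arm. Then 1342 / 0.90 = 1491.1, rounded up to 1492. Both match the protocol.

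With 1500 per arm:

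- Planned difference: 0.504 − 0.450 = 0.054, or 0.054 × 1500 = 81 patients.
- One net patient misclassified in one arm: 1/1500 = 0.067 percentage points, or 1/81 = 1.2% of the planned effect.

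The protocol allows 10% overall for loss to follow-up but gives no rate for 6.2.1 withdrawals. The net counts below are therefore assumptions, shown only to give a scale. They are differences between arms in misclassified patients, not numbers of withdrawals.

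| Assumed net excess in one arm | Shift if misclassified as independent | Shift if the same patients, not independent, leave the cohort |
|---|---|---|
| 0 | 0 | 0 |
| 5 | 5/1500 = 0.33 points | 675/1495 − 0.45 = 0.15 points |
| 15 | 15/1500 = 1.0 point | 675/1485 − 0.45 = 0.45 points |

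The 675 is 0.45 × 1500. As illustration only, with SE = √(2 × 0.45 × 0.55 / 1500) = 0.01817, a misclassification shift of 0.33 or 1.0 point would raise the type I error from 5.0% to 5.4% or 8.5%. These figures assume all 1500 per arm are analysed and carry no weight in the conclusion.

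**The case against.** The strongest reply is that 6.2.1 lists triggers and that 7.6 and 7.7 are the procedure. A patient withdrawn under 6.2.1 has also stopped study drug for good, so 7.6.2 and 7.6.3 apply. In 7.6.3, follow-up ends only when the patient refuses all contact and withdraws consent; no route lets an investigator end it. Since 7.7 uses study withdrawal loosely enough to include a drug stop, the two sections can be reconciled. Item 1 is discretionary, and poor compliance conflicts only through a heading. Harm further requires that no useful mRS is taken at the discontinuation visit, that the carried value falls on the wrong side of 2, and that the net error differs by arm in a double-blind trial. Carrying values forward is also a separate design choice.

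Much of this stands. It shows the probable intent, and it rules out any claim about the size of the bias. It does not make the text consistent: the reconciliation has to be inferred from a loose use of words in 7.7 that 7.6.2 contradicts, and 6.2.1 does not point to either section.

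A reader might go further and infer that the protocol orders visits to stop after an SAE or worsening. It does not; 6.2.1 is silent. A reader might also infer that the triggering SAEs drop out of the safety data. They do not: 10.5 and 10.6 record them and count patients who did not complete the trial.

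**Conclusion.** The inconsistency is real and should be fixed. Section 6.2.1 uses study withdrawal for events that 7.6.2 treats wholly or partly as drug discontinuation, and no section expressly secures the month-3 mRS after a 6.2.1 withdrawal. Continued follow-up is probably intended, so the risk lies in how sites apply the text.

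The size of any bias cannot be determined: there is no withdrawal rate, no stated content for the discontinuation visit, and no information on balance between arms. The sign is not fixed either, because items 1 and 2 tend towards wrongly carried successes while items 4 to 6 can produce wrongly carried failures. It would be tempting to conclude that the rule favours XST or inflates the type I error. The documents do not support that; the bias is zero if the errors balance. The conclusion rests only on the wording and on the link between the first two grounds and the primary outcome.

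**What to change.** - Reword 6.2.1 so that its events lead to discontinuation of study drug under 7.6. The clinical decision stays with the investigator. Refer poor compliance to 7.6.2.
- Add that month-3 and month-12 mRS, SAEs and vital status are collected in all randomised patients unless the patient withdraws consent for follow-up.
- Align 7.7 with 7.6.2, so that stopping the drug is no longer an example of leaving the study.

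The analysis does not need these patients withdrawn: section 13.1.2 already names poor compliance among the usual major violations for the per-protocol cohort, with the exact definition left to data review. The cost is a wording amendment and a site instruction. The month-3 and month-12 visits are already scheduled for every patient.
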